## Methods/design

### Participants

The parents of healthy children aged 1 to 5 years presenting to seven *TARGet Kids!* participating academic pediatric or family medicine group practices in Toronto, Canada for a scheduled well-child visit prior to viral season (September through November over four years) are being approached to participate. Practices have between 3 and 10 practicing physicians. We are excluding children with gestational age < 32 weeks as they are a high risk population for respiratory tract infection and asthma, children with chronic illness (except for asthma) on parental report which is known to interfere with vitamin D metabolism and increase the risk of respiratory infection, and those children with a sibling participating in the study to reduce clustering effects.

After parents of participating children provide informed consent, baseline characteristics are obtained using a parent-completed, standardized, data collection form based on questions used in the Canadian Community Health Survey (see Additional file 2: Baseline Data Collection Form) [86]. The following data is being collected: age, sex, birth weight, enrolment date, parents’ ethnicity, maternal age, education and health, duration of breastfeeding, bottle use, current and past vitamin D supplementation, dietary vitamin D intake using 3 day dietary recall, daily multivitamin use, influenza immunization status, screen viewing time, physical activity, outdoor time, and sun exposure. In addition, height, weight and skin pigmentation are being measured using standardized techniques. A venous blood sample is obtained to document baseline 25-hydroxyvitamin D levels.

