### Intervention

Children are randomly assigned to one of two groups: ‘standard dose’ of 400 IU/day vitamin D or ‘high dose’ of 2000 IU/day vitamin D (see Figure 1). A drop-based formulation (Kids Ddrops™ containing Vitamin D3) was chosen to facilitate ease of administration to young children. Parents of children in each group are instructed to administer 1 drop of the provided solution to their child by mouth once daily, at any time of day, each day from the time of enrolment (September-November) through the winter until follow-up (April-May) 4–8 months later. As 25-hydroxyvitamin D levels are reported to stabilize within 8 weeks [91,92], and respiratory viruses tend to circulate in Canada November through April [93], children are recruited September through November. The duration of the intervention (4–8 months) has been chosen to mimic the routine practice of vitamin D supplementation of preschoolers over the Canadian winter (see Table 1).

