### Outcomes and measures

The *primary outcome* is the number of laboratory-confirmed viral URTIs per child over the winter months. Because of the wide variety of respiratory viruses and URTI illness presentations, signs and symptoms of viral URTI are non-specific and may not be reliably measured by parental report [95,96]. Therefore, in addition to parents of enrolled children completing a symptom checklist with each URTI (see Additional file 3: Symptom Checklist), parents are asked to obtain a nasal swab from their child. Nasal swabs done by parents have been shown to be as effective in detecting respiratory viruses as those obtained by health professionals but less invasive and better tolerated [97]. Parents are instructed to place the swab in provided viral transport media and refrigerate until couriered to the study laboratory (Mount Sinai Services) within 24 hours [44,98]. Respiratory viruses are identified using reverse transcriptase polymerase chain reaction (RT-PCR) technology. RT-PCR is performed on each sample which has a sensitivity of 95% and specificity of 100% for the identification of respiratory RNA viruses, which is more sensitive than viral culture and comparable to immunofluorescence [99]. Samples are tested for 18 common respiratory viruses including influenza A and B, adenoviruses, respiratory syncytial virus (RSV), picornaviruses (enteroviruses and rhinoviruses), coronovirus, metapneumovirus and parainfluenza virus using the ID-Tag™ RVP assay using the Luminex xMAP™ system (Cat# R019A0105, TM Bioscience Corp., Toronto, ON) [100]. This is the same assay and machine that is routinely used in the Ontario public health laboratories.

*Secondary outcomes* include parent reported URTI, specific viral agents that cause URTI (influenza, adenovirus and RSV), asthma exacerbations among children with asthma, physician-diagnosed otitis media and pneumonia, emergency department visits and hospitalizations, collected by monthly telephone call and confirmed by review of the child’s clinic medical record. Follow-up 25-hydroxyvitamin D serum level is measured to determine the vitamin D dose vs. serum response relationship. Finally, change in 25-hydroxyvitamin D serum level from baseline is determined to document that an improvement in health outcomes is mediated through an increase in 25-hydroxyvitamin D serum level.

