### Recruitment and retention

Since June 2008, over 4500 children age 1–5 years have been recruited through *TARGet Kids!* practices with collection of questionnaires (demographics, lifestyle factors) and anthropometric measures (height, weight and waist circumference). Since December 2008 venous blood samples have been collected from over 2500 children [107]. *TARGet Kids!* is now operating out of seven sites with over 100 children per month being recruited with phlebotomy. Therefore, recruitment of 750 children in September through November over 4 consecutive seasons for this study is feasible.

We expect that there will be a different spectrum of infections as respiratory virus incidence, distribution and severity tend to vary from year to year.

Strategies to achieve adequate recruitment include approaching eligible subjects during a well-child visit. Lists of children scheduled for a well-child visit are reviewed in advance. An information package is mailed to each family 2 to 4 weeks prior to the visit inviting them to participate. This allows parents time for consideration in advance and reduce coercion to participate. Parents are approached in person by the research assistant while registering for the clinic visit. At the initial visit, baseline survey data, anthropometric measures, and baseline vitamin D serum level are collected.

Strategies for retention include a monthly telephone call to encourage collection of nasal swabs and completion of symptom checklists. Every reasonable attempt is made to locate patients at follow-up. Topical anesthetic cream (EMLA or Ametop) is offered to minimize discomfort from venipuncture. Blood is drawn in the primary care physician’s office negating the need to attend a separate laboratory visit. Parents who have moved out of district are offered to visit The Hospital for Sick Children for repeat laboratory testing. Should these efforts fail to obtain a blood sample, a home visit for phlebotomy is offered. This is expected to occur in less than 10% of subjects.

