### Follow-up data collection and data management

Parents of participating children receive a monthly telephone call by a research assistant reminding them to administer the vitamin D supplement daily and record the number of asthma exacerbations, emergency department visits, hospitalizations and missed work days. Parents are also be reminded to collect nasal swabs and complete symptom checklists. In addition, parents are asked to return to their child’s physician’s office in April or May to capture peak respiratory virus season. At the follow-up visit, blood is drawn for 25-hydroxyvitamin D level and a follow-up data collection form completed. The following potential co-interventions are also measured: influenza vaccination, dietary vitamin D intake using a 3 day dietary recall [86], over-the-counter vitamin and mineral supplementation (i.e., calcium containing multivitamins), herbal remedies (i.e., echinacea) and hours per week in daycare (see Additional file 4: Follow-up Data Collection Form). This methodology has been used successfully by our group and others [44,45,98].

To ensure high quality data collection, research assistants are trained in the accurate completion of questionnaires, anthropometric measurement and are registered pediatric phlebotomists as per standard *TARGet Kids!* operating protocol. Weight is measured using a precision digital scale (±0.025% SECA, Hamburg Germany), standing height is measured using a stadiometer (SECA, Hamburg Germany), and skin pigmentation is measured using a narrow-band reflectometer (Dermaspectrometer, Cortex Technology) [108-111]. Questionnaires and URTI symptom checklists have been pilot tested to ensure understandability and reduce incomplete responses [101]. Collected data is electronically entered on a daily basis by research assistants at each site into the study’s central database via a secure web-based data portal.

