### Statistical analysis

Baseline characteristics will be summarized by appropriate descriptive statistics. Although randomization is expected to balance the covariates, variables that demonstrate, by chance, a potentially clinically meaningful imbalance, will be considered as possible adjusting covariates.

All outcomes will be analyzed following the *intention-to-treat* principle [113]. The primary analysis of the primary outcome will assess the effect of vitamin D supplementation on laboratory-confirmed URTI. Mean URTI rates (per child) will be computed for each group. A Poisson regression model will be used to make the statistical comparison between the groups. *Variable length of follow-up time* will be accounted for by using a suitable offset (logarithm of observation duration) in the Poisson model. If there is evidence of overdispersion, a negative-binomial model may be considered. The secondary analysis of the primary outcome will use survival methods to examine time to first URTI and the Andersen-Gill extension of the Cox model to analyze recurrent URTI events [114]. The rationale for conducting the trial over four seasons is to increase the chance of a sufficiently active viral season to assess a protective effect of the intervention. This will also allow us to examine the consistency of the effect over the four seasons as strains of viruses vary from year to year.

Analysis of secondary outcomes will use standard methods for continuous data (i.e., vitamin D level) using means, ANOVA and linear regression with and without adjustment for baseline group differences. The incidence of binomial secondary outcomes such as specific viral infections will be summarized descriptively. Since the incidence of some infections may be low, logistic regression analyses will only be performed to assess the treatment effect when there are sufficient events (over 30). Subgroup analyses will be conducted for children with asthma. Frequency of asthma exacerbations will be analyzed using the same methods as those used for the primary outcome.

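### The rise in 25-hydroxyvitamin D can show that the arms separated, not that it mediated any fall in URTIs; secondarily, baseline level should be a fixed covariate rather than one that depends on chance imbalance

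*Protocol article*

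**What the plan says.** Two places in the protocol article matter.

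**Purpose of the serum measurement.** Under Outcomes and measures, the change from baseline "is determined to document that an improvement in health outcomes is mediated through an increase in 25-hydroxyvitamin D serum level". The baseline draw is described twice: under Participants ("A venous blood sample is obtained to document baseline 25-hydroxyvitamin D levels") and under Recruitment and retention, where at the first visit "baseline survey data, anthropometric measures, and baseline vitamin D serum level are collected". The later draw is at the April-May visit: "At the follow-up visit, blood is drawn for 25-hydroxyvitamin D level and a follow-up data collection form completed" (Follow-up data collection and data management). Under Intervention, "respiratory viruses tend to circulate in Canada November through April". Table 1 places laboratory-confirmed URTI in the September-March column.

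**Analysis of the level.** Under Statistical analysis, continuous secondary outcomes such as vitamin D level are to be analysed "using means, ANOVA and linear regression with and without adjustment for baseline group differences". The same section sets the covariate rule: "variables that demonstrate, by chance, a potentially clinically meaningful imbalance, will be considered as possible adjusting covariates". Neither the adjusted nor the unadjusted version is named as the main one. Randomisation is stratified by practice site (Intervention).

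**The concern.** The mediation sentence states an inference, not just a measurement. Mediation is a claim that the rise in level caused the fall in URTIs. Randomising dose supports a causal statement about dose on level and about dose on URTI. It does not support one about level on URTI, because children whose levels rise more or less within an arm are not randomised to do so. Reading the level after most URTIs have been counted adds a further problem: illness, appetite and adherence during the winter may themselves move the level.

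Explaining the causal relationship is a stated secondary goal of the trial (Study design). The background also faults an earlier trial in schoolchildren because, without serum levels, its benefit could not be attributed to a rise in level. A reader could therefore take measured levels here as settling the mechanism.

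The second matter is smaller. Whether baseline level predicts follow-up level does not depend on whether the arms happen to differ at baseline. Tying adjustment to an observed difference gives up precision that is available at no cost, and leaves two results with no stated order.

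**Working it through.** The article gives no SD, power or correlation for 25-hydroxyvitamin D, so there is no figure of its own to reproduce. The correlation *r* between baseline and follow-up level is an assumption throughout. The number analysed is 300 per group (Sample size: 375 recruited, 20% loss, 375 × 0.80 = 300).

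**1. What the serum change can show**

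- Dosing starts at enrolment in September-November and the follow-up level is drawn in April-May. URTIs accrue before or up to that draw. The text describes one baseline and one follow-up level. Table 1 as extracted marks the level under September-March and April-May, but its layout may be broken and the text is clear.
- The change also has a seasonal part. The background says there is little skin production from November to March north of 42°N, and Toronto is at 43°N. Baseline therefore precedes the winter fall, and an April-May draw may include some renewed sun. Randomisation balances this between arms, but it adds variation between children within an arm.

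Two simulated cases (300 per group, 500 trials each, effects assumed) have no path from serum level to URTI:

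| Case | Arm difference in change | URTI rate ratio | Pooled change-URTI association significant | Within-arm association significant |
|---|---|---|---|---|
| Treatment raises level by 1 SD and lowers URTI (mean 4 to 3) by another route | 1.0 SD | 0.75 | 81% | 5.4% |
| Treatment raises level by 1 SD, has no effect on URTI, and each URTI lowers the later level by 0.1 SD | 1.0 SD | 1.00 | 99.6% | 100% (mean correlation -0.20) |

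The arm difference in change is the same in both. In the first case the pooled association arises only because arm drives both variables; a within-arm analysis would correctly show nothing. In the second, even the within-arm analysis is misled, because the level is read after the outcome.

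**2. What fixing the baseline covariate gains**

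With equal SDs at the two times, variance of the arm comparison relative to unadjusted ANOVA is 1 - r² for ANCOVA and 2(1 - r) for the change score.

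| r (assumed) | ANCOVA | Change score | ANCOVA n per group equal to 300 unadjusted |
|---|---|---|---|
| 0.3 | 1 - 0.09 = 0.91 | 1.40 | 300 × 0.91 = 273 |
| 0.5 | 1 - 0.25 = 0.75 | 1.00 | 300 × 0.75 = 225 |
| 0.6 | 1 - 0.36 = 0.64 | 0.80 | 300 × 0.64 = 192 |

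A chance baseline difference of 0.1 SD shifts the unadjusted estimate by 0.1 × r, which is 0.03 to 0.06 SD over this range.

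**3. Error rates**

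In 20,000 simulated null trials, each analysis alone had about 5% type I error. Adjusting only when the baseline difference exceeded 0.1 SD (an assumed threshold, met in about 22% of trials) gave 4.9% at r = 0.3 and 3.6% at r = 0.5. An imbalance rule of this kind is therefore conservative: it wastes precision rather than inflating error.

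**The case against.** **On mediation.** The protocol reports that levels stabilise within 8 weeks, and dosing continues to follow-up. That is a fair reason to treat the April-May level as a proxy for the winter level on treatment, and it stands. It means the late draw is not by itself fatal, but a good proxy for exposure still does not turn arm separation into evidence of mediation.

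A reader might infer that mediation would be declared automatically from any dose-response in serum level. The text does not support this: the sentence presupposes an improvement in health outcomes, so a rise in level without fewer URTIs would document nothing under it. It is also a purpose clause, with no test or decision rule attached and no mediation objective listed. What remains is that if URTIs did fall, for whatever reason, the sentence would assign the cause.

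**On adjustment.** Unadjusted ANOVA is valid under randomisation, and reporting unadjusted and adjusted results together is ordinary. Linear regression with adjustment is already listed, and the baseline differences meant could include baseline level. So it cannot be said that precision is certainly lost.

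A reader might also infer inflated type I error from having two versions. The simulated rate is about 6.6% to 8.1% for r from 0.3 to 0.7, but only if either result may be claimed, and the protocol states no such rule.

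The gain may also change no conclusion. With 300 per group, an unadjusted comparison has 80% power at about 2.80 × √(2/300) = 0.23 SD, and the doses differ fivefold. Choice of the lead model for a secondary outcome can often be left to an analysis plan. The point here is narrower: the rule the article does state, adjustment driven by imbalance, is a weaker choice than one that costs nothing.

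**Conclusion.** The mediation statement is wrong as written and should be corrected. Given the randomised factor, the timing of the single follow-up draw and the absence of any described mediation analysis, the change in level can document separation between arms and no more. This rests on the design, not on the simulation, whose assumed effects only illustrate it.

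The adjustment point is an improvement, not an error in validity. Its size is a variance reduction of about 9% to 36% for r from 0.3 to 0.6; the documents give no r. It concerns a secondary outcome on which the arms are likely to separate clearly. The primary URTI comparison, the sample size and the conduct of the trial are unaffected.

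**What to change.** - In Outcomes and measures, replace the mediation purpose with: *to document the separation in serum level between arms*. Label any association between level and URTI exploratory.
- In Statistical analysis, make the main comparison of follow-up 25-hydroxyvitamin D a linear regression (ANCOVA) on arm, with baseline level and stratification site fixed in advance whatever the observed imbalance. Report the unadjusted result as supportive.
- Follow-up draw date need not be a required covariate, because it is determined after randomisation.

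The cost is wording only. The baseline level and site are already planned for every child, and no new sample, visit or participant is needed.

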### Economic analysis

A cost-effectiveness analyses will be conducted using data from this trial. A societal perspective will be employed to calculate both direct health service utilization costs as well as indirect costs to families of an URTI. The time horizon of the analysis will be limited to the follow-up of this trial in order to leverage direct data. Given the short time horizon, discounting of costs and outcomes will not be applied. This analysis will include the cost of ‘high dose’ vitamin D supplementation, physician visits, medications (antimicrobial and over-the-counter), hospital admissions, emergency department visits and laboratory testing abstracted from the child’s medical record and costs associated with lost income from parental work absenteeism and time out of daycare obtained by monthly telephone call using previously described techniques [45,74,115]. Standard, publicly available costing sources will be used to cost resource utilization parameters. Specifically, we will use cost sources such as the Ontario Health Insurance Programs (OHIP), Ontario Case Costing Initiative (OCCI) and standard Ministry of Health (MOH) reimbursements for diagnostic tests. Sex-weighted hourly wage rate will be derived from Statistics Canada Data. The cost-effectiveness analysis will estimate the cost per laboratory-confirmed URTI avoided. The net benefit regression approach will be used to determine each patient’s net benefit from treatment (NB_
*i*
_) based upon the data collected on resource use and lost parental productivity [116]. Graphs will be used to illustrate the incremental net benefit assuming varying willingness to pay. Each estimate of net benefit will be adjusted for potential confounders through regression. In its simplest form, net benefit regression involves fitting the following simple linear regression model: NB_
*i*
_ = β_0_ + β_TX_TX_
*i*
_ + ϵ_
*i*
_ where TX_
*i*
_ is the *i*^th^ person’s treatment indicator (TX_
*i*
_ = 1 for new treatment and 0 for usual care) and ϵ_
*i*
_ is a stochastic error term [117]. Parametric confidence intervals for incremental net benefit will be compared to results of non-parametric bootstrapping to characterize statistical uncertainty in the economic analysis.

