### Recommended vitamin D serum levels and supplementation for preschoolers

It is well established that 25-hydroxyvitamin D serum levels above 50 nmol/L in children are sufficient to prevent rickets [6]. Therefore, the American Academy of Pediatrics (AAP) suggests that 25-hydroxyvitamin D levels in children be above 50 nmol/L [4]. Data from adults suggest that serum levels above 75 nmol/L are required to minimize calcium resorption from bone and maximize intestinal calcium absorption [26]. Therefore, the Canadian Paediatric Society (CPS) suggests that optimal 25-hydroxyvitamin D level for children is above 75 nmol/L [5].

The recommended vitamin D dietary allowance (RDA) for children older than 1 year has been set at 600 IU/day by both Health Canada and the Institute of Medicine. Because children who consume less than 1000 ml of vitamin D fortified cow’s milk per day (which includes most preschoolers) [3,27] are unlikely to receive this amount of dietary vitamin D, the AAP recommends routine vitamin D supplementation of 400 IU/day for all children ingesting < 1000 ml/day of vitamin D-fortified formula or cow’s milk [4]. The CPS has no recommendation for routine vitamin D supplementation for Canadian children older than 1 year [5]. However, we have found that 56% of our population is receiving 400 IU/day of supplemental vitamin D [28,29]. To reflect the current AAP recommendation and common practice in our population, we chose 400 IU/day for the ‘standard dose’ arm.

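### The economic cost list names only the high-dose supplement; applied as written, it leaves the standard-dose supplement uncosted and shifts the result against high dose by that product's cost

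*Protocol article*

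**What the plan says.** The trial has two active arms: "Children are randomly assigned to one of two groups: ‘standard dose’ of 400 IU/day vitamin D or ‘high dose’ of 2000 IU/day vitamin D" (Intervention). Both use a supplied product in the same way: "Parents of children in each group are instructed to administer 1 drop of the provided solution to their child by mouth once daily". Use runs from enrolment in autumn to follow-up in spring, 4–8 months.

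The Economic analysis section sets the viewpoint: "A societal perspective will be employed to calculate both direct health service utilization costs as well as indirect costs to families of an URTI". It then lists the cost items: "This analysis will include the cost of ‘high dose’ vitamin D supplementation, physician visits, medications", followed by hospital and emergency care, laboratory tests, lost parental income and time out of daycare. No item is given for the standard-dose supplement. The planned outputs are the cost for each laboratory-confirmed URTI averted and a net benefit regression. In its simplest form, that regression has a treatment indicator coded "1 for new treatment and 0 for usual care".

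**The concern.** Every other item on the list applies to both groups. The supplement item carries the label of one group. An analyst who builds each child's cost from this list would charge the high-dose children for their drops and the standard-dose children nothing. The effect side would compare 2000 IU/day with 400 IU/day, while the cost side would compare a paid-for supplement with a free one.

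Nothing else on the list clearly picks up the missing cost. The Intervention section prohibits other vitamin D products during the trial, and Ethical considerations says that families receive the trial supplement free. The standard-dose drops would therefore not be expected to surface as a family expense or as an over-the-counter medication in the medical record.

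The supplement is also the only listed cost that can differ between the groups by design. All the others differ only if the dose changes illness. The smaller the effect on URTI, the more the economic result depends on how the supplement is costed.

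**Working it through.** The article gives no supplement price, incremental cost or cost-effectiveness ratio, so there is no figure of its own to reproduce. The check is an accounting identity.

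**Inputs**
- Both arms take a supplied drop daily (Intervention).
- The only supplement cost named is that of the high-dose product (Economic analysis).
- Design effect: four URTIs per child reduced by one, so d = 1 URTI avoided per child (Sample size).
- Cost of a URTI in preschoolers: $261 to $276 (Background, Viral upper respiratory tract infection).
- Not in the document: cH and cS, the per-child costs of the high-dose and standard-dose supplements.

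**Step 1: incremental cost.** Let ΔO be the difference in all other costs.
- List applied as written: cH − 0 + ΔO.
- Like for like: cH − cS + ΔO.
- Difference: cS per child.

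**Step 2: net benefit regression.** For each child, net benefit is willingness to pay times effect, minus cost. Omitting cS raises the mean net benefit of the standard-dose group by cS, so the treatment coefficient falls by cS whatever the willingness to pay. A simulated check used 300 children per arm, Poisson means of 4 and 3, and assumed costs cH = 20 and cS = 15. The coefficient shifted by −15.0 at willingness to pay of 0, 50 and 200. The planned graphs, parametric intervals and bootstrap would all carry this shift, so none of them would reveal it.

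**Step 3: cost per URTI avoided.** The overstatement is cS/d:
- d = 1: cS
- d = 0.5: 2 × cS
- d = 0.25: 4 × cS

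**Step 4: share of the high-dose price.** The price ratios are assumptions.

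| cS/cH | Incremental supplement cost as written | Like for like | Overstatement |
|---|---|---|---|
| 0.25 | cH | 0.75 cH | 25% of cH |
| 0.50 | cH | 0.50 cH | 50% of cH |
| 0.75 | cH | 0.25 cH | 75% of cH |
| 1.00 | cH | 0 | 100% of cH |

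**Step 5: scale in dollars, for illustration only.** Assume cS between $5 and $30 per child per winter; the document gives no such figure.
- At d = 1 the overstatement per URTI avoided runs from 5/276 = 1.8% to 30/261 = 11.5% of the cost of one URTI.
- At d = 0.25 it is four times as large: 20/276 = 7.2% to 120/261 = 46.0%.
- If both products cost the same and each URTI avoided saves $261–$276, the literal list turns a saving into a net cost only when d is below cS divided by the saving. For $30 that is 30/276 = 0.11 to 30/261 = 0.11; for $5 it is 5/276 = 0.018 to 5/261 = 0.019. These are far below the design effect of 1.

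**The case against.** The strongest reply is that the section says what the analysis will include; it does not say that nothing else will be included. It neither excludes the standard-dose product nor sets its cost to zero. In an incremental analysis the phrase could be shorthand for the added cost of the high dose. The document is also a condensed article, and unit prices and the assignment of costs to arms are normally left to a fuller plan. This stands as far as it goes: a reader might infer that the comparator's supplement will definitely be left out and the result will definitely be biased, and the text does not support that. But the words name the cost of the high-dose supplement, not its extra cost, and a cost input tied to one arm is something the article states, not a detail it leaves out.

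A reader might also take "1 for new treatment and 0 for usual care" as evidence that the comparator is costed as no supplement. It is not. The phrase belongs to a generic description of the regression, and in a two-arm trial the zero group can only be the 400 IU/day arm. Nor would the label justify a zero cost, because the Background reports that "we have found that 56% of our population is receiving 400 IU/day of supplemental vitamin D".

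Finally, no harm is locked in. The analysis is secondary, no price is given to show that a conclusion would change, and the comparator's price can be added without new patient data. All of this stands. It limits the importance of the point but not its direction.

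**Conclusion.** The point holds conditionally. If the cost list is applied as written, incremental cost is overstated and incremental net benefit understated by cS, the per-child cost of the standard-dose supplement, and the cost per URTI avoided is overstated by cS/d. The direction, against high dose, follows from the arithmetic provided that the standard-dose product costs something. As a share of the high-dose product's cost, the error lies between 0% (standard dose costs nothing) and 100% (both cost the same), assuming that the standard-dose product is not the dearer of the two.

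The dollar size cannot be derived from the article. At the design effect it may well be small beside the cost of a URTI; it matters most if the trial finds little or no effect. The primary outcome, the sample size and the error rates are untouched. The plan needs a correction to a cost input; there is no demonstrated bias in a result.

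**What to change.** State in the Economic analysis section that the trial supplement is costed in both groups, at each product's own price and over each child's duration of use. The treatment coefficient then carries only the high-dose minus standard-dose difference in supplement cost. If the phrase was meant as the added cost of the high dose, say so.

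As a minor matter of wording, describe the zero level of the treatment indicator as the 400 IU/day group.

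The cost is one sentence and one extra price. No new patient data are needed, since bottles are already returned at the end of the trial to calculate the amount given. The change can be made at any time before the economic analysis is run.
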